#### Handling of Missing Data

Where a single day of IMV data are missing but has been received on the previous and next day, it will be assumed that it was also received on the missing day. No IMV will be assumed on the day of hospital discharge unless otherwise recorded.

For the interim analysis, a complete case analysis will be presented (including only patients with complete data after the above assumptions). Additional sensitivity analyses will be performed under two different scenarios: IMV is provided on all missing days for patients in the permissive MAP target arm and not provided for all missing days for patients in the usual care arm, and vice versa.

For the final analysis where IMV data are missing, last observation carried forward will be applied while the patient is known to remain in PICU. For the adjusted analysis, levels of missingness of baseline variables will be assessed, and imputed if necessary.

Imputation will use the Multivariate Imputation using Chained Equations algorithm, with the model including all baseline variables included in the adjusted models, and the model including all outcome and baseline variables included in the sensitivity analysis. The number of imputations will be determined according to level of missingness. Models will be fitted in each imputed dataset and results combined using Rubin’s rules. If the levels of missingness in baseline data are deemed to be too high, the relevant baseline variable may be excluded from the analysis.

Analysis of change in functional status will use patients with non-missing data only and repeated with missing data imputed among patients known to be alive at those time points.

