### Clinical Effectiveness Analysis Methods

#### Primary Outcome

The primary clinical outcome will be summarized by arm (median, IQR, graphically) and analyzed using a two-sample rank-sum (Wilcoxon-Mann-Whitney) test (10). The primary effect estimate will be the probabilistic index, the probability that intervention is superior to control for the composite outcome, and 95% CI. The separate components will also be presented by arm with effect sizes and 95% CIs, following established guidelines (11). Mortality will be analyzed using logistic regression, adjusting for age (younger than1 yr; 1 yr to younger than 3 yr; 3 yr or older), and site as a random effect. Duration of IMV will be analyzed using a two-sample rank-sum test.

Ordered logistic regression will estimate the proportional odds ratio, adjusting for baseline variables. The unadjusted OR will be presented for comparison. If data completeness allows, the following variables will be used in adjusted analyses: predicted log odds of mortality at randomization (Paediatric Index of Mortality, version 3 [PIM-3] score (12) [continuous; linear]); primary reason for admission (suspected/proven infection vs. other); comorbidities (neurologic vs. non-neurologic vs. none); age (continuous; restricted cubic splines with four knots at the 5th, 35th, 65th, and 95th percentiles); and site (random effect).

Baseline covariates were prespecified based on anticipated associations with the outcomes. Results will be reported as adjusted odds ratios with 95% CI.

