#### Subgroup Analyses

If sample sizes allow and following established guidelines (13, 14), subgroup analyses will test for interactions between treatment allocation and baseline covariates: age (continuous); infection (proven/suspected; none); comorbidities (neurologic vs. non-neurologic vs. none); PIM-3 score (continuous).

Where data completeness is below an acceptable threshold, multiple imputation may be used, or the relevant subgroup removed. The Instrument to Assess the Credibility of Effect Modification Analyses tool will assess the credibility of subgroup findings (15).

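### The main imputation model for baseline covariates leaves out the outcome; if the subgroup analyses also use it, their interaction estimates shrink toward zero

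*SAP article*

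**What the plan says.** Under Primary Outcome, the SAP article supplements the rank-sum test with an adjusted model: "Ordered logistic regression will estimate the proportional odds ratio, adjusting for baseline variables". The covariates are PIM-3 log odds, reason for admission, comorbidities, age and site.

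Handling of Missing Data then provides: "For the adjusted analysis, levels of missingness of baseline variables will be assessed, and imputed if necessary". It describes two chained-equations specifications in one sentence. The first is for the adjusted models, "with the model including all baseline variables included in the adjusted models". The second is "the model including all outcome and baseline variables included in the sensitivity analysis". Neither mentions allocation. There is also a way out: "If the levels of missingness in baseline data are deemed to be too high, the relevant baseline variable may be excluded from the analysis".

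Under Subgroup Analyses, "subgroup analyses will test for interactions between treatment allocation and baseline covariates": age, infection, comorbidities and PIM-3. For incomplete data that section says: "Where data completeness is below an acceptable threshold, multiple imputation may be used, or the relevant subgroup removed". It names no imputation model and does not point to Handling of Missing Data.

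**The concern.** The two specifications are contrasted within one sentence. Outcome is listed in the second and not in the first, so its absence from the first reads as a choice rather than shorthand.

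A covariate imputed without the outcome is, in the imputed records, unrelated to the outcome given the other predictors. When those records are pooled with the observed ones, the covariate's own effect is diluted, and so is any interaction between it and treatment. This happens even when data are missing completely at random. The analysis that would come first gets the imputation model that conflicts with the analysis model, and the sensitivity analysis gets the compatible one.

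At stake are the prespecified interaction tests. Imputation is an option there exactly when completeness is poor, which is when dilution is greatest. A real difference in effect by severity, infection or comorbidity would look smaller than it is.

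The document describes a route to such missingness. Admission data come through linkage to the national audit (Baseline Patient Characteristics). If record access is declined, linkage does not take place, but primary outcome data are still collected (Consent). A child can therefore have an outcome and no linked baseline data. How often this will happen is not stated.

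**Working it through.** **The plan's own figures.** The plan gives no missingness rate and no imputation-related figure to reproduce. Its one design figure is 90% power with 1,900 randomized. With 10% loss, 1,900 × 0.90 = 1,710 are analysed. Simulating the rank-sum test with deaths ranked worst, and an SD of 9.5 days in both arms, gives power of 0.87-0.88 at 1,710 and 0.90-0.92 at 1,900. That is close to the stated figure. Nothing below depends on it except the choice of n = 1,710.

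**Step 1: expected size in a linear model.** Let a standardised covariate x have correlation ρ with another baseline variable z, and let a fraction m be missing completely at random. Values imputed from z alone are x* = ρz + e*, where e* is unrelated to the outcome. Let x̃ be x where observed and x* where imputed.

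- Effect of x adjusted for z: only the observed fraction carries the residual association, so the estimate is (1 − m) times the truth.
- Interaction with a balanced randomized treatment, in a model with a common z slope: the estimate is E[x·x̃] = (1 − m) + mρ² = 1 − m(1 − ρ²) times the truth.

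With ρ = 0.3 (assumed), 1 − ρ² = 0.91, so the interaction attenuation is 0.91m.

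**Step 2: simulation of the interaction under baseline-only imputation.** All runs assume the missingness rates shown. The linear run used n = 1,710, ρ = 0.3, 5 imputations and 200 replicates. Logistic run A used n = 1,710, 300 replicates, a covariate log-OR of 0.8, an interaction log-OR of 0.3 and ρ = 0.3. Logistic run B was a separate check, also with a binary stand-in for the ordinal model.

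| Missing | Formula 0.91m | Linear run | Logistic run A | Logistic run B |
|---|---|---|---|---|
| 5% | 4.6% | 4% | 8% | 6% |
| 10% | 9.1% | 9% | 16% | 12% |
| 20% | 18.2% | 20% | 31% | 26% |
| 30% | 27.3% | 26% | 42% | 41% |

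The linear run agrees with the formula; the logistic runs show more attenuation. As an example, in run A at 20% missing the interaction log-OR falls from 0.307 with full data to 0.212. That is a ratio of odds ratios of exp(0.307) = 1.36 reported as exp(0.212) = 1.24 per SD of the covariate.

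**Step 3: which omission matters.** Run A, estimates as a fraction of the full-data value:

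| Missing | Covariate effect, baseline only | Interaction, baseline only | + allocation | + allocation and outcome | + their product |
|---|---|---|---|---|---|
| 5% | 0.94 | 0.92 | 0.92 | 0.95 | 0.99 |
| 10% | 0.88 | 0.84 | 0.84 | 0.90 | 0.97 |
| 20% | 0.76 | 0.69 | 0.69 | 0.80 | 0.96 |
| 30% | 0.65 | 0.58 | 0.57 | 0.71 | 0.93 |

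Allocation alone changes nothing. Adding outcome and allocation restores the covariate effect (0.99-1.00) but only part of the interaction. The product term recovers most of the rest.

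**Step 4: the adjusted treatment effect.** In run A the treatment log-OR, full data against baseline-only imputation, was −0.090 and −0.089 at 5%, −0.108 and −0.105 at 10%, −0.093 and −0.088 at 20%, and −0.093 and −0.089 at 30%. The largest shift is 0.005 (odds ratio 0.911 against 0.916), with an empirical standard error of about 0.12.

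**The case against.** The strongest reply is that the subgroup section does not adopt this model. It makes imputation optional, allows the subgroup to be removed instead, and may leave the model to a fuller plan. That stands, and it makes the subgroup consequence conditional. It does not remove the point: the article specifies no other chained-equations model, so an analyst who imputes a subgroup variable would most likely use this one.

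Second, the adjusted analysis targets the treatment odds ratio, not the covariate coefficients. Randomization makes covariates independent of allocation, so imputing baseline data from baseline data is defensible for that purpose. This stands in full. A reader might infer that the primary result or the adjusted treatment effect is biased; neither is, to any extent that matters.

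Third, a reader might infer that the plan ignores the outcome throughout, or that leaving out allocation is the cause. The document supports neither. The outcome is in the sensitivity version, the absence of allocation is inferred from silence, and adding allocation alone had no effect. The sensitivity version gives little protection here, however. The clinical Sensitivity Analyses section covers only adherence and a per-protocol fallback, not the adjusted or subgroup models.

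Fourth, imputed values are not wholly unrelated to the outcome, because some association survives through correlated covariates. The ρ² term above is that part.

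Finally, the higher missingness rates may never apply, since such variables can be dropped. Age is a stratification factor and should be complete.

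**Conclusion.** The concern holds in a limited form. Read naturally, the main imputation model for the adjusted analyses omits the outcome. The primary test is untouched and the adjusted treatment odds ratio essentially so. If the same model is used for incomplete PIM-3, infection or comorbidity data, a true interaction is attenuated roughly in line with the missing fraction or somewhat more: about 4-8% at 5% missing, 9-16% at 10% and 20-31% at 20%. The risk is understating real effect modification; where there is none, this mechanism does not create it.

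The sizes rest on assumed missingness rates, data missing completely at random, a single continuous covariate with assumed effects, and linear or binary logistic stand-ins for the planned ordinal model. The direction was the same in every run; the exact percentages should not be relied on. This is worth correcting before unblinded analysis, but it does not threaten the trial's main conclusion.

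**What to change.** In Handling of Missing Data, change the main chained-equations model so that it includes allocation, all analysis covariates and the outcome, meaning the primary score with death as worst or whichever outcome is being modelled. For interaction analyses, impute separately by arm or add allocation-by-outcome terms. Outcome and allocation without the product left the interaction at 0.80 of its full-data value at 20% missing. In Subgroup Analyses, state that this is the model used if a subgroup variable is imputed.

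Baseline-only imputation can be kept as a sensitivity analysis for the adjusted treatment effect, where it does no harm. The cost is a sentence or two in the plan and slight extra coding. No new data are needed, and the sample size and primary analysis do not change.

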### Cost-Effectiveness Analysis Methods

#### Cost-Effectiveness Analysis

The cost-effectiveness analysis (CEA) will use patient-level data on resource use and outcomes from multiple sources: CRFs, PICANet data, and follow-up questionnaires (health services and HrQoL).

The CEA will adopt a health and personal health services perspective as recommended by NICE recommendations (17) and will measure use of resources required to deliver the intervention, length of stay in PICU and acute hospital, for the index admission and any readmissions within 12 months, and use of personal health services after acute hospital discharge within 12 months postrandomization. Resource use data will be valued using appropriate unit costs data from the NHS Payment by Results database, and unit costs of health and social care (Personal Social Services Research Unit), to calculate total costs up to 12 months.

QALYs will be calculated from responses to Pediatric Quality of Life Inventory (PedsQL) questionnaire which will be mapped onto the Child Health Utility 9D (CHU-9D) index score using an appropriate mapping function (18). The mapped CHU-9D index score will be combined with survival data to calculate QALYs. QALYs at 12 months postrandomization will be calculated by valuing each patient’s survival time by their HrQoL (as indicated by the mapped CHU-9D utility score) at 12 months, using the “area under the curve” approach (19). For 12 months survivors, QALYs will be calculated using the CHU-9D scores at 12 months, assuming HrQoL of zero at randomization, and a linear interpolation between randomization and 12 months. For nonsurvivors to 12 months, a zero QALY will be assumed for the 12-month period.

The CEA will follow ITT principle and will use appropriate regression methods. The interclass correlation coefficient (ICC) will be calculated which measures the proportion of the overall variation at the cluster level. If ICC greater than 10%, multilevel models (MLMs) will be used to handle clustering and avoid potential biases and incorrect inferences. The CEA model will adjust for key baseline covariates as per the primary clinical analysis. Missing data in health economic endpoints will be handled with appropriate multiple imputation methods, assuming the data are missing at random conditional on the observed data (20). On the imputed datasets the CEA will use a Bivariate Seemingly Unrelated Regression model to allow for correlation between costs and QALYs (21). The incremental results from multiply-imputed datasets will be summarized using Rubin’s rule (22).

The CEA will report the mean (95% CI) incremental costs, QALYs and net monetary benefit at 12 months. Results uncertainty will be summarized and represented on a cost-effectiveness plane and using acceptability curves. The CEA will report results for the overall patient group and subgroups as per the primary clinical analysis.

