## METHODS

### Trial Design and Randomization

PRESSURE is a pragmatic, multicenter, parallel group, superiority randomized controlled trial. Eligible patients are randomized to either usual care or the permissive MAP target arm (age-dependent target). Allocation is by randomized permuted blocks with variable block lengths, stratified by site and age category (younger than 12 mo; 1 yr to younger than 3 yr; 3 yr or older).

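### The base-case cost-effectiveness model brings in site, a randomisation stratum, only if an estimated ICC exceeds 10%; below that its intervals can be modestly too wide

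*SAP article*

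**What the plan says.** - **Randomisation** (Trial Design and Randomization): "Allocation is by randomized permuted blocks with variable block lengths, stratified by site and age category". The unit of allocation is the patient, not the site.
- **Clinical models** (Clinical Effectiveness Analysis Methods, Primary Outcome): the logistic model for mortality adjusts for age group "and site as a random effect". The covariate list of the adjusted ordered logistic model ends with age as a spline "and site (random effect"). Neither carries an ICC condition. The primary test itself is an unadjusted two-sample rank-sum test.
- **Base-case economic model** (Cost-Effectiveness Analysis): an ICC is calculated, and then "If ICC greater than 10%, multilevel models (MLMs) will be used to handle clustering and avoid potential biases and incorrect inferences". The following sentence reads "The CEA model will adjust for key baseline covariates as per the primary clinical analysis". After imputation, "the CEA will use a Bivariate Seemingly Unrelated Regression model to allow for correlation between costs and QALYs".
- **What is reported**: "The CEA will report the mean (95% CI) incremental costs, QALYs and net monetary benefit at 12 months", with acceptability curves.
- **Sensitivity analysis** (Cost-Effectiveness Analysis Methods, Sensitivity Analysis, item 4): single-level and multilevel results are to be compared, with no ICC condition.

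**The concern.** The rule treats site as a nuisance that matters only when clustering is strong. In this design site is a stratum that the randomisation balances. The variance of the treatment contrast is therefore smaller than a model without site reports, at any ICC above zero. A model that omits site gives standard errors and intervals that are too large for the allocation actually used.

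Two further features make the rule a poor one to fix in advance. First, the base case is chosen by an ICC estimated from 21 sites, which is imprecise. Second, the article does not say whether the ICC is that of costs, QALYs or net benefit, or what follows if costs and QALYs, which are modelled jointly, fall on opposite sides of 10%. The headline intervals and the acceptability curve depend on that choice.

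**Working it through.** **Inputs from the article.** 21 sites (abstract, Setting); allocation stratified by site and age category; 1900 randomised with 10% allowed for withdrawal or refusal (Sample Size), so 1900 × 0.9 = 1710 analysed; two-sided 5% level and 95% intervals (CIs and p Values); ICC threshold 10%.

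**The plan's own figure.** The article gives no ICC, standard deviation or precision target for costs or QALYs, so there is no economic design figure to reproduce. The clinical sample size does reproduce. With 855 per arm, mortality 13% vs 11%, SD 9.5 d in both arms and the full 18-hour reduction (mean 7.8 to 7.05 d), 10,000 simulated rank-sum tests gave power of 0.914 (continuous days) or 0.908 (whole days), against the stated 90%. It serves here only to supply the 1710.

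**Assumed.** ICCs from 1% to 10%; a common treatment effect across sites; no between-site variation absorbed by other covariates.

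**Step 1: excess width when site is omitted.** Set the total variance to 1 and the between-site part to ICC. With arms balanced within site, the treatment contrast carries only the within-site variance, 1 − ICC. The model without site uses the total. Hence

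reported SE / correct SE = 1/√(1 − ICC)

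true coverage = 2Φ(1.96/√(1 − ICC)) − 1

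| ICC | Width ratio | Coverage of nominal 95% CI | Effective two-sided alpha |
|---|---|---|---|
| 1% | 1/√0.99 = 1.005 | 95.1% | 0.049 |
| 2% | 1/√0.98 = 1.010 | 95.2% | 0.048 |
| 5% | 1/√0.95 = 1.026 | 95.6% | 0.044 |
| 8% | 1/√0.92 = 1.043 | 95.9% | 0.041 |
| 10% | 1/√0.90 = 1.054 | 96.1% | 0.039 |

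**Step 2: check by simulation.** 21 sites of unequal size, about 1710 patients, permuted blocks of 2, 4 or 6 within site and age stratum (block lengths, site sizes and age mix assumed), 3,000 trials per ICC. The ratio of mean SE without site to mean SE with site was 1.009 at ICC 2%, 1.024 at 5% and 1.050 just under 10%. At the last value the mean reported SEs were 0.0482 without site and 0.0459 with it, while the unadjusted estimate actually varied with an SE of 0.0450. Coverage was 96.3% without site and 95.6% with it. Formula and simulation agree: the intervals are too wide, not too narrow.

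**Step 3: how steady is the trigger?** Take 21 equal sites of 81 patients (1701 in all), normal data, and the ANOVA estimate ICC = (MSB − MSW)/(MSB + 80 × MSW), where MSB and MSW are the between-site and within-site mean squares. In 200,000 draws per value:
- True ICC 7%: the estimate exceeds 10% in 11% of trials.
- True ICC 10%: the middle 95% of estimates runs from about 4.5% to 16.6%, and the rule selects the multilevel model in 46% of trials.
- True ICC 13%: the rule fails to select it in 24% of trials.

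Skewed costs and unequal sites would probably make the estimate less steady.

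**Step 4: does the covariate sentence bring site in anyway?** The clinical list includes site, so a literal reading puts site in the base case and makes the ICC rule redundant. If the covariates meant are the patient-level ones, the ICC sentence governs site. Both readings are available, and Step 1 applies only under the second.

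**The case against.** The best defence is that the harm is small, conservative and already visible. The sensitivity analysis compares single-level and multilevel results whatever the ICC, so readers will see both. The excess is capped, because above the threshold the multilevel model takes over, and near 10% the two models differ by only about 5% in standard error. The adopted covariates may absorb some site variation. All of this stands and keeps the point minor. It does not remove it: the reported base-case intervals and acceptability curve still depend on the threshold.

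Four stronger readings are tempting, and the document supports none of them.
- **Intervals too narrow.** The ICC sentence, with its reference to incorrect inferences, may suggest the cluster-trial problem. Allocation here is by patient within site, so omitting site errs the other way.
- **A contradiction within the paragraph.** The covariate sentence can be read with or without site, so this is an ambiguity. Nor can one claim both that site is in the covariate set and that the intervals are too wide.
- **Economic results out of line with clinical ones because of site.** The primary clinical test does not adjust for site, and several secondary outcomes use unadjusted Fisher or rank-sum tests. The clinical results already mix both approaches.
- **A loss of some 190 patients.** A 10% information loss applied to 1900 gives that figure, but it holds only at the threshold, and 1900 includes the withdrawal allowance; on 1710 it is 171. The economic analysis has no precision target against which to count such a loss.

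**Conclusion.** The point holds as a minor one. Under the reading in which the ICC rule governs site, the base-case intervals for incremental costs, QALYs and net benefit are wider than the design warrants by about 1.0% at ICC 2%, 2.6% at 5% and at most about 5.4% just under 10%. Coverage then rises to at most about 96.1%. The cap applies to the outcome whose ICC is used as the trigger, and the article does not name that outcome.

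The result rests on assumed ICCs, a common treatment effect across sites and no absorption of site variation by the other covariates, so the figures are upper values for each ICC. The direction is conservative, and no false claim of cost-effectiveness is made more likely. What remains is an avoidable loss of precision, a base case picked by a noisy estimate, and an unclear statement of whether site is among the adopted covariates.

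**What to change.** Delete the 10% rule. State that site enters both the cost and the QALY equations of the base case, as a random or fixed effect, whatever the ICC, alongside the age term already in the adopted covariate set. Report the ICCs for costs and QALYs descriptively. Keep the single-level model as the sensitivity analysis, which reverses the roles of two models the plan already intends to fit.

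The cost is a few lines of SAP wording. No new data are needed, and the multilevel model is already planned in the economic sensitivity analysis.
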